### Secondary endpoint

The secondary endpoint, during the study follow-up, will be the graduation of anginal symptoms and also of heart failure. Cardiac decompensation hospitalization will be considered a secondary event

### Ambulatory follow-up

All patients will have periodic outpatient follow-up as described in Table 2. This follow-up will be independent of the treatment group to which the patient was allocated, and participants will be followed in close outpatient visits. All patients and families were given a telephone number of the study coordinating center in case of doubts or any clinical minor or major event. This close follow-up will permit good retention rates and a complete follow-up. Neurological evaluation will be available to patients after surgery and, if necessary, at follow-up. Cardiological evaluation will be done throughout the follow-up. No biological specimens will be collected in this study.

**Table 1 Tab2:** Schedule of the study, with all detailed assessments for each study period

	Study period								
	Enrollment	Allocation	Post-allocation					Close- out	
**Timepoint****	***Interview***	**Rand**	**1 M**	**6 M**	**12 M**	**24 M**	**36 M**	**48 M**	**60 M**
**Enrollment**	X								
**Eligibility screen**	X								
**Informed consent**		X							
**Allocation**		X							
**Angiograms**		X							
**History/events**	X	X	X	X	X	X	X	X	X
**Anginal assessment**	X	X	X	X	X	X	X	X	X
**Dyspnea assessment**	X	X	X	X	X	X	X	X	X
**Medicines**	X	X	X	X	X	X	X	X	X
**ECG**	X		X		X	X	X	X	X
**Echocardiography**	X		X						X
**Laboratory**	X				X	X	X	X	X
**Interventions:**									
***Surgery***			X						
***Angiograms***									X
**Assessments:**									
***Follow-up***			X	X	X	X	X	X	X
***CT angiography***									X
***Neuropsychological Tests***			X						X
***ECG stress tests***					X				X
***Quality of life***	X			X	X	X	X	X	X
***Costs and effectiveness***			X						X
***Working status***			X						X

*M* month, *ECG* electrocardiogram. Laboratory tests will include creatinine, LDL-cholesterol, glycated hemoglobin, CK-MB, troponin, and BNP levels

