### Quality of life

Quality of life of treatment related to the health of patients will be evaluated in the entire population of the patients of MASS-VI (HF). Quality of life related to symptoms as well as the functional status of patients will be assessed through a combination of generic and disease-specific measures selected to cover a wide range of potential health domains that may be affected by coronary artery disease, their treatments, and complications. The SF-36 Questionnaire will be used to evaluate patient condition [10].

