### Cost-effectiveness—working condition

The use of this resource using a global health classification that reflects a patient’s preference for his or her current health status in relation to perfect health are particularly important outcome measures for the cost-effectiveness analysis [11]. Use of resources and health care with hospital cost data will be collected prospectively from admission to discharge and remain for a 5-year follow-up for all patients, including all costs associated with the interventional procedure. For each revascularization procedure, the detailed use of resources will be collected through a standard case report form. Use of medical follow-up resources (including hospitalization, outpatient services, and cardiovascular medications) will be evaluated through detailed questionnaires that will be completed during each scheduled patient contact.

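### SF-36 has no assessment between enrollment and 6 months, so a temporary loss during surgical recovery is not seen; if SF-36 feeds the cost-effectiveness analysis, the comparison could favor surgery

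*Protocol article*

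**What the plan says.** All of this is in the protocol article.

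- **Schedule, Assessments block.** The row "Quality of life" is marked at enrollment, 6, 12, 24, 36, 48 and 60 months, and is empty at randomization and at 1 month. The follow-up row has a mark at 1 month and at every later visit. "Costs and effectiveness" and "Working status" are each marked at 1 and 60 months only. Neuropsychological tests are also marked at 1 month.
- **Schedule, Interventions block.** Surgery is marked in the 1-month column and nowhere else.
- **Schedule, upper block.** History/events, the anginal assessment and the "Dyspnea assessment" are marked at every time point, including 1 month.
- **Quality of life.** Health-related quality of life "will be assessed through a combination of generic and disease-specific measures", but only one instrument is named: "The SF-36 Questionnaire will be used to evaluate patient condition".
- **Cost-effectiveness—working condition.** The outcome for the economic analysis is described separately, as "a global health classification that reflects a patient’s preference for his or her current health status in relation to perfect health". No instrument is named for it. Costs run from admission through 5 years, "including all costs associated with the interventional procedure".
- **Statistical analysis.** The economic comparison is to estimate differences in effect over both the short and the long term.

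**The concern.** The two strategies should differ most in quality of life during the weeks around the operation. Under Surgical treatment, every operation uses extracorporeal circulation. The medical arm has no planned counterpart. Yet the one named instrument jumps from enrollment to 6 months, and a loss that opens after surgery and closes before 6 months leaves no trace in that series.

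Two things make this more than a matter of taste. First, the protocol undertakes to estimate short-term effect differences, and a first post-baseline SF-36 at 6 months cannot show a short-term difference in quality of life. Second, costs and health effects may be treated unequally: the money cost of the operation is collected in full, while a temporary health cost on the SF-36 scale is not. If SF-36 were then turned into utilities and interpolated, the omission would act in one direction, toward the arm that the trial is designed to show superior.

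**Working it through.** The document states no figure for this point, so there is none to reproduce. The check has two parts.

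**1. Schedule rows side by side**

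| Row | Enrollment | 1 month | 6 months | Later visits |
|---|---|---|---|---|
| Quality of life | yes | no | yes | 12, 24, 36, 48, 60 |
| Follow-up visit | no | yes | yes | 12, 24, 36, 48, 60 |
| Surgery | no | yes | no | none |
| Costs and effectiveness | no | yes | no | 60 |
| Working status | no | yes | no | 60 |

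The gap is confirmed: patients are seen at 1 month, and quality of life is not recorded there.

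**2. Size of the loss that would be missed, if SF-36 supplies utilities and they are interpolated**

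Inputs:
- Visit times of 0, 1 and 6 months, from the schedule.
- Dip *d* at month 1, measured below the straight line from enrollment to 6 months. The document gives none. Assumed 0.05, 0.10 and 0.20.
- For illustration, a utility of 0.60 at enrollment and 0.70 at 6 months, also assumed. These cancel out of the result.

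Area over 0 to 6 months, in QALY:
- Points at 0 and 6 months only: (0.60 + 0.70)/2 × 0.5 = 0.325.
- Points at 0, 1 and 6 months with *d* = 0.10: the line at month 1 is 0.60 + 0.10/6 = 0.6167, so the utility there is 0.5167. The area is (0.60 + 0.5167)/2 × 1/12 + (0.5167 + 0.70)/2 × 5/12 = 0.0465 + 0.2535 = 0.300.
- Difference: 0.325 − 0.300 = 0.025.

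In general the difference is a triangle with a base of half a year and height *d*: 0.5 × 0.5 × *d* = 0.25*d*. If recovery is complete by 3 months, the base is a quarter of a year: 0.5 × 0.25 × *d* = 0.125*d*.

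| Assumed dip *d* | Missed loss, recovery by 6 months (0.25*d*) | In quality-adjusted days (× 365) | Missed loss, recovery by 3 months (0.125*d*) |
|---|---|---|---|
| 0.05 | 0.0125 | 4.6 | 0.006 |
| 0.10 | 0.025 | 9.1 | 0.0125 |
| 0.20 | 0.05 | 18.2 | 0.025 |

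Each figure is per surgical patient.

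**The case against.** The best case against the point has five parts.

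- **SF-36 may not be the effectiveness input.** The economic section describes a preference-based classification without naming it, other quality-of-life measures are promised, and the schedule marks costs and effectiveness at 1 month. A utility may be taken then. This stands, and it makes any bias conditional. It does not close the gap in SF-36 itself. Moreover, that row has only the 1-month and 60-month marks, so a utility taken there would have no enrollment value and nothing in between, and the SF-36 series might well be needed to fill it.
- **No QALY or interpolation rule is stated, and such rules belong in an analysis or health-economic plan.** True of the method. But when data are collected is fixed here, and no later plan can recover a questionnaire that was not given.
- **Early harm is partly captured.** Death, infarction and stroke are primary events, and events, angina, dyspnea, neuropsychological tests and working status are all recorded at 1 month. This stands: only a transient loss on the SF-36 scale goes unrecorded. Nor is such a loss strictly confined to the surgical arm, since medical-arm patients may need an intervention for unstable angina.
- **A 1-month form might miss the loss.** Surgery shares the 1-month column, so the form could come before the operation or very soon after it. This stands and shapes the fix.
- **One extra point does not give the shape of recovery.** If recovery is complete by 3 months, a straight line from 1 to 6 months would count 0.25*d* where the loss is 0.125*d*. This also stands, but with a 1-month value the assumption can at least be varied.

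A reader might go further and infer that effectiveness is biased toward surgery as a matter of fact, by a large share of the benefit. For example, a 5-point survival gain building linearly over 5 years at utility 0.7 is worth 0.5 × 5 × 0.05 × 0.7 = 0.0875 QALY, of which 0.025 is 29% (14% to 57% across the dips). The document does not support this. It does not say that SF-36 supplies effectiveness. Every term in the ratio is assumed. The denominator also leaves out any gain from relief of symptoms, which the Discussion presents as the expected effect of correcting ischemia, so the ratio is inflated.

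**Conclusion.** The gap is real and is in the stated schedule: SF-36 has no point between enrollment and 6 months, although patients attend at 1 month and surgery falls in that interval. A temporary loss that resolves by 6 months is therefore not seen, which sits badly with the undertaking to estimate short-term effects.

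Bias in the cost-effectiveness comparison is possible but not established. It needs SF-36 as the source of effectiveness and interpolation from enrollment to 6 months. On those conditions the error would favor surgery, by about 0.0125 to 0.05 QALY per surgical patient for assumed dips of 0.05 to 0.20, or about 0.006 to 0.025 if recovery is complete by 3 months.

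The analysis concerned is ancillary. The primary endpoint and SF-36 comparisons at each visit from 6 months on are untouched. This is a cheap improvement, not a serious defect.

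**What to change.** Add SF-36 at the 1-month visit in both arms. Give it at a fixed interval after the operation, with a matched time in the medical arm. If the visit has to stay on the randomization clock, record the time since operation on the form. State which instrument supplies the effectiveness values, use the new assessment in that calculation, and vary the assumed date of full recovery (for example 3 and 6 months) as a sensitivity analysis.

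The cost is one short questionnaire per patient at a visit that is already scheduled. It will be missing for the few patients already past that visit; under Trial status, three patients had been enrolled at first submission and recruitment was expected to run until mid-2024.

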### Ancillary studies

The quality of life with application of the SF-36 questionnaire and the cost-effectiveness evaluation between the two types of treatment will be applied with outpatient follow-up for 5 years.

### Quality of life

Quality of life of treatment related to the health of patients will be evaluated in the entire population of the patients of MASS-VI (HF). Quality of life related to symptoms as well as the functional status of patients will be assessed through a combination of generic and disease-specific measures selected to cover a wide range of potential health domains that may be affected by coronary artery disease, their treatments, and complications. The SF-36 Questionnaire will be used to evaluate patient condition [10].

### Cost-effectiveness—working condition

The use of this resource using a global health classification that reflects a patient’s preference for his or her current health status in relation to perfect health are particularly important outcome measures for the cost-effectiveness analysis [11]. Use of resources and health care with hospital cost data will be collected prospectively from admission to discharge and remain for a 5-year follow-up for all patients, including all costs associated with the interventional procedure. For each revascularization procedure, the detailed use of resources will be collected through a standard case report form. Use of medical follow-up resources (including hospitalization, outpatient services, and cardiovascular medications) will be evaluated through detailed questionnaires that will be completed during each scheduled patient contact.

### Statistical analysis

Patients eligible for the MASS-VI (HF) study will be invited to attend the Heart Institute– FMUSP outpatient clinic to receive additional information. Candidates for surgical treatment when admitted will be visited by one of the study doctors. After giving consent, patients will be randomized. To ensure a reasonable balance of the sample, the assignment is made according to a computer-generated list of randomly permuted blocks that are unknown to the investigators. The generation of the allocation sequence is in the statistics department without the possibility of access to researchers.

After randomization, patients will be scheduled for the intended treatment. The design is open label with only outcome assessors being blinded, so unblinding will not occur. The objective of the main analysis is to compare the results of the primary events of this study. Kaplan-Meier curves will be used for graphical comparison of the data. All values will be expressed as mean ± standard deviation or percentage. The continuous variables will be compared by the Wilcoxon test, whereas the variables will be analyzed with the Fisher exact test. The occurrence of event results will be compared using the Cox proportional hazards model, reflecting a risk rate. The analysis of the primary objectives will be based on the intention-to-treat principle. Interim analyses will be conducted annually to assess safety. For both treatment strategies, the cost of diagnostic procedures, treatment procedures, complications, and short- and long-term effect differences will be estimated. Marginal costs in monetary terms will be calculated by multiplying unit costs and marginal medical consumption as recorded for each patient.

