## Methods/Design

A total of 600 patients with angina pectoris will be screened for conventional coronary artery disease with obstructive lesions ≥ 70% of the arterial lumen and left ventricular dysfunction; 300 patients will be randomized to myocardial revascularization surgery, and another 300 patients will receive drug treatment. Patients who have been victims of acute myocardial infarction (AMI) in the previous 6 months, are on dialysis, or have disabling degenerative disease will not be included. In addition, patients who refuse to sign a consent form or who do not accept a possible surgical randomization will not be included. The stages of randomization are described in Fig. 1 (Patient selection flowchart). This is a study performed at an Academic Hospital. All data for inclusion, follow-up, and occurrence of events will be collected in a single center in Brazil.

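### The only comparison rule for continuous variables is the Wilcoxon test, and per-patient cost is not exempted, although the planned cost-effectiveness comparison needs the difference in mean cost

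*Protocol article*

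**What the plan says.** The Statistical analysis section of the protocol article states how values are summarised, "All values will be expressed as mean ± standard deviation or percentage", and then how they are compared: "The continuous variables will be compared by the Wilcoxon test, whereas the variables will be analyzed with the Fisher exact test". No other method for a continuous variable is named, and no variable is exempted.

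After the sentences on the Cox model, intention to treat and interim analyses, the same section turns to cost: "For both treatment strategies, the cost of diagnostic procedures, treatment procedures, complications, and short- and long-term effect differences will be estimated". It then says how cost is formed: "Marginal costs in monetary terms will be calculated by multiplying unit costs and marginal medical consumption as recorded for each patient". Cost is therefore a continuous amount recorded for each patient.

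Under Ancillary studies, "the cost-effectiveness evaluation between the two types of treatment will be applied with outpatient follow-up for 5 years". Under Cost-effectiveness—working condition, cost data run from admission to discharge and "remain for a 5-year follow-up for all patients, including all costs associated with the interventional procedure". Under Methods/Design, "300 patients will be randomized to myocardial revascularization surgery, and another 300 patients will receive drug treatment".

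**The concern.** A cost-effectiveness comparison turns on arithmetic mean cost, because only the mean multiplied by the number of patients gives the total spend under each strategy. The Wilcoxon test has a different target. Its null hypothesis is that the two distributions are identical, and it responds to the probability that a patient in one arm costs more than a patient in the other. It speaks to means only when the two distributions have the same shape.

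Here the shapes are likely to differ. Operated patients all carry the cost of the index operation. Patients on drug treatment do not, and some of them may have expensive admissions or later procedures. If the rule is applied to cost, the operation cost lifts most surgical patients in the ranking however much a minority of drug-treated patients later consume. The article could then report mean costs that point one way and a p-value that points the other.

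**Working it through.** **Plan's own figure.** None is stated for the cost comparison, so there is nothing to reproduce. From the article come 300 patients per arm and the 5% level. Every cost and event-frequency input below is an assumption.

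**Step 1: one case by hand.** Assume surgical costs centred on a mean of 20. Assume drug-arm costs with a base mean of 5, plus a mean of 70 in 30% of patients.
- Mean drug cost = 5 + 0.30 × 70 = 26, against 20 for surgery, so drug treatment is 30% dearer.
- The 70% of drug patients without the extra cost rank almost entirely below the surgical patients, and the other 30% almost entirely above. P(surgical cost > drug cost) is therefore about 0.70.
- Under the Wilcoxon null this probability is 0.50, with standard error √[(300 + 300 + 1)/(12 × 300 × 300)] = √(601/1,080,000) = 0.0236.
- z ≈ (0.70 − 0.50)/0.0236 ≈ 8.5, in the direction of surgery being costlier.

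In 4,000 simulated trials of this case, Wilcoxon declared surgery costlier in 100%. Welch did so in 0% and declared drug treatment costlier in 80%.

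**Step 2: equal true means, range of assumptions.** The unit is the mean cost of the index operation.
- Surgical cost = index cost (lognormal, mean 1, CV 0.4) + routine care (lognormal, mean b, CV 0.5) + a costly event with probability ps (lognormal cost, mean c, CV 0.6).
- Drug cost = the same without the index cost, and with event probability pm.
- Difference in means, surgery minus drug = 1 − (pm − ps)c. Setting c = 1/(pm − ps) makes it zero, which gives c = 1/0.20 = 5 or c = 1/0.30 = 3.3.

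Share of 2,000 trials in which two-sided 5% Wilcoxon rejects, essentially always towards surgery being costlier:

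| b | (ps, pm) = (.10, .30) | (.20, .40) | (.20, .50) | (.25, .55) |
|---|---|---|---|---|
| 0.5 | 100% | 100% | 93% | 74% |
| 1 | 100% | 99.8% | 77% | 50% |
| 2 | 99% | 77% | 29% | 16% |

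Welch rejects in 4.6% to 6.0% of the same trials. Independent reruns agree within simulation error: 15% to 100% for Wilcoxon and about 4% to 7% for Welch.

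**Step 3: drug arm truly dearer by 0.5 unit.** Set c = 1.5/(pm − ps), so the difference is 1 − 1.5 = −0.5. Share in which Wilcoxon significantly favours surgery being costlier:

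| b | (.10, .30) | (.20, .40) | (.20, .50) | (.25, .55) |
|---|---|---|---|---|
| 0.5 | 100% | 100% | 71% | 34% |
| 1 | 100% | 99% | 33% | 13% |
| 2 | 95% | 55% | 2% | 0.7% |

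The reversal fades as costly events become common in both arms and routine care dominates.

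**Step 4: different shapes only, no event model.** Both arms are lognormal with equal means and log-SD 0.4 for surgery. With drug-arm log-SD 0.6, 0.8 and 1.0, Wilcoxon declares surgery costlier in 65%, 99% and 100% of trials. Welch rejects in either direction in 4.6%, 4.7% and 6.4%. When the two distributions are identical (log-SD 0.8 in both), Wilcoxon declares surgery costlier in 2.6% and drug treatment costlier in 2.1%, so it holds its level. The distortion comes from the difference in shape.

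**The case against.** The strongest reply is that the article does not say that costs will be tested with Wilcoxon. The Wilcoxon and Fisher sentence follows the one on descriptive summaries. Cost comes later, in its own sentences, where costs are to be estimated, with no test or p-value attached. Those sentences can be read as a separate estimation exercise, with its details in a plan that is not shown. This stands: the link to cost is an inference from an unqualified rule, and a missing bootstrap specification would not by itself be a fault in a condensed article. What remains is that the one comparison rule in print, read literally, covers a per-patient continuous cost in a planned between-treatment evaluation.

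A second reply concerns size, and it also stands. The costs and event frequencies are assumed. The article's only event figure is 9% in the medical arm, with no time horizon, for an endpoint that leaves out heart-failure admissions. If 9% were the full frequency of costly events and the surgical arm had none, equal means would need an event cost of 1/0.09 ≈ 11 index operations. If surgery is in truth dearer on average, the ranks and the means would normally agree in direction.

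Third, the design guarantees an index cost for operated patients only. The high-cost tail in the drug arm is plausible but assumed; both arms receive optimal medical therapy and can have later events.

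A reader might therefore infer that the trial will report a false cost conclusion, or that the design makes the shapes differ. The documents support neither. They show that a mismatch is possible, not how likely or how large it is.

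**Conclusion.** The point holds as a minor one. The stated rule for continuous variables does not exempt cost, and if it is applied to cost it answers a different question from the one a cost-effectiveness comparison asks. Under assumed costs with equal true means, surgery is wrongly declared costlier in roughly 15% to 100% of trials with 300 per arm, against a two-sided rejection rate of about 5% for a comparison of means. That range rests wholly on assumed cost distributions with different shapes. With similar shapes the distortion would be small, and the actual size cannot be known from the article. Cost is an ancillary outcome, so the primary endpoint and its Cox analysis are untouched.

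**What to change.** Add one sentence to the Statistical analysis section that exempts cost from the Wilcoxon rule. It should state that five-year cost per patient is compared by intention to treat as the difference in arithmetic mean cost, with a 95% confidence interval from a non-parametric bootstrap that resamples patients within each arm (or from Welch's method). The same bootstrap can serve the joint cost and effect difference. The Wilcoxon test can stay for the other continuous variables. If a separate analysis plan already names a method based on means, a cross-reference to it is enough.

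This needs no new data, patients or procedures. The downside is that an interval for mean cost can be wide when costs are skewed, so a cost difference may look less certain than a rank-test p-value would suggest.

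### The only tests named for non-event outcomes are unadjusted Wilcoxon and Fisher, so enrollment angina, dyspnea and quality-of-life values go unused, and Fisher, if applied to grades, would also discard their order

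*Protocol article*

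**What the plan says.** - **Tests for non-event variables** (Statistical analysis): "The continuous variables will be compared by the Wilcoxon test, whereas the variables will be analyzed with the Fisher exact test". The word giving the type of the second group of variables is missing; categorical is the likely meaning. No test is assigned to a named endpoint. No baseline-adjusted, ordinal or repeated-measures method is mentioned.
- **Secondary endpoint**: "the graduation of anginal symptoms and also of heart failure". These are ordered grades; the scales are not named. The section adds: "Cardiac decompensation hospitalization will be considered a secondary event".
- **Quality of life** (Ancillary studies): "The quality of life with application of the SF-36 questionnaire" is planned over 5 years. It is an ancillary outcome and not part of the listed secondary endpoint.
- **Schedule table** (Ambulatory follow-up): angina and dyspnea are assessed at enrollment, at randomization and at 1, 6, 12, 24, 36, 48 and 60 months. Quality of life is assessed at enrollment and at 6, 12, 24, 36, 48 and 60 months.
- **Events** (Statistical analysis): "The occurrence of event results will be compared using the Cox proportional hazards model, reflecting a risk rate". Kaplan-Meier has a display role: "Kaplan-Meier curves will be used for graphical comparison of the data". Death as a competing event for admissions is not mentioned.

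**The concern.** The protocol does not leave the non-event analysis wholly open. It names two tests, and neither can take a covariate. Each symptom and quality-of-life outcome has a value recorded before treatment starts, and patients who begin worse will tend to stay worse. A comparison that ignores that value leaves explainable variation in the error term.

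The second issue is conditional. An angina or heart-failure grade is ordered. Fisher's exact test on a table of several grades treats a shift of one grade like any other rearrangement of the counts, so it spreads its power over patterns of no clinical interest.

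Neither test by itself yields an adjusted treatment difference with a confidence interval, which is what a reader wants from a symptom endpoint. This matters because the protocol's Discussion presents symptom relief as an expected result of correcting ischemia, and the design is open label, so the size of a symptom effect will be examined closely.

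A smaller matter concerns heart-failure admissions. Death prevents a later admission. An absolute risk taken as one minus the Kaplan-Meier estimate (1-KM), with the dead censored, exceeds the proportion of patients who are actually admitted.

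**Working it through.** **Inputs.** The protocol states no effect size, baseline correlation, grade distribution or hazard for these outcomes, so there is no figure of its own to reproduce on this point. The one number taken from it is the required total in Sample size calculation: 585 at 1:1 gives 585/2 = 292.5, taken as 292 per arm. Everything else below is assumed. Alpha is taken as 5%, two-sided.

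**1. Ignoring the enrollment value (continuous score).** Assume a true difference of 0.2 SD, normal data, and correlation r between enrollment and follow-up score. Adjustment multiplies the variance by 1 − r².

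- Unadjusted: z = 0.2/√(2/292) = 2.417, so a t-type comparison has power Φ(2.417 − 1.96) = 68%. For normal data Wilcoxon has efficiency 3/π, giving Φ(2.417 × √(3/π) − 1.96) = 66%.
- Adjusted: power = Φ(2.417/√(1 − r²) − 1.96).

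| r | 1 − r² | Equivalent gain in patients, 1/(1 − r²) | Adjusted power, formula | Adjusted (ANCOVA), simulated | Wilcoxon, simulated |
|---|---|---|---|---|---|
| 0.3 | 0.91 | 1.10 | 72% | 73% | 67% |
| 0.5 | 0.75 | 1.33 | 80% | 80% | 65% |
| 0.7 | 0.51 | 1.96 | 92% | 92% | 65% |

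The simulations used 2,000 runs per row and agree with the formulas. The loss is about 6 to 27 power points. About 2 of these points come from Wilcoxon against a normal-theory test on normal data and not from the missing baseline.

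**2. Ignoring order (four grades).** Assume control-arm grades of 35/35/20/10% and a common odds ratio. At 1.5 the other arm becomes 44.7/33.1/15.3/6.9%. An unordered chi-square test stands in for Fisher's exact test, and the rank test is Wilcoxon (4,000 runs).

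| Odds ratio | Unordered test | Rank test |
|---|---|---|
| 1.4 | 43% | 60% |
| 1.5 | 61% | 77% |

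A repeat with another random seed gave 44% against 62% and 58% against 75%. With 250 per arm, grades of 25/40/25/10% and an odds ratio of 1.5, the repeat gave 52% against 69%. In every case the gap is about 17 or 18 points. It arises only if grades are sent to Fisher. If they are ranked by Wilcoxon, order is kept and only the loss in step 1 remains.

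**3. Absolute risk of admission (minor).** Assume constant hazards per year, h for admission and d for death. At 5 years, 1-KM = 1 − exp(−5h). Cumulative incidence = h/(h + d) × [1 − exp(−5(h + d))].

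| h | 1-KM | d = 0.04 | d = 0.06 | d = 0.09 |
|---|---|---|---|---|
| 0.05 | 22.1% | 20.1% | 19.2% | 18.0% |
| 0.08 | 33.0% | 30.1% | 28.8% | 26.9% |

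The overstatement is about 2 to 6 percentage points. It shrinks with lower mortality. The protocol assumes 9% for the whole primary composite in the medical arm, with no time horizon. If that were a 5-year figure and every event a death, d = −ln(0.91)/5 = 0.0189, and at h = 0.08 cumulative incidence would be 31.6% against 33.0%, a gap of 1.4 points.

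**The case against.** **The link from test to endpoint is inferred.** The quoted sentence is generic, lacks a word, and follows a sentence on reporting means and percentages, so it can be read as a rule for descriptive tables. This stands, and it is why the point about order is conditional. The point about enrollment values does not depend on it, because neither named test uses them whichever way the grades are assigned. Change scores are not excluded, but they are not mentioned either.

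**Endpoint-level models usually sit in the full protocol or SAP.** True, and their absence from an article would not be a finding. Here the article names the tests, so the comment is on a stated choice for which a better one exists using data already scheduled.

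**The unadjusted tests are valid, and estimates may still be reported.** Both hold. A reader might infer biased symptom comparisons; randomization rules that out as a consequence of omitting baseline. Naming a test also does not forbid reporting a difference.

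**A stronger reading on admissions is tempting.** A reader might infer that heart-failure admissions will be compared by Kaplan-Meier with the dead kept at risk. The document does not say so. It assigns Kaplan-Meier to graphs and event comparisons to Cox, and the surrounding text concerns the primary composite, which already contains all-cause death. Cox with censoring at death gives a valid cause-specific hazard ratio. Only an absolute admission risk read from a 1-KM curve, if one is shown, would be too high.

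**The suggested models have their own difficulty with death.** A repeated-measures model can treat scores after death as merely missing, and a proportional-odds model needs a rule for patients who have died. This stands, so the rule must be stated.

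**Conclusion.** The point holds as a matter of efficiency for the secondary symptom endpoint and the ancillary SF-36 outcome. It does not touch the primary analysis or the validity of any test. The part on enrollment values is firm: they are scheduled, and the named tests leave them out. The part on order holds only if grades are analysed by Fisher.

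The cost is about 6 to 27 power points for unused baseline at correlations of 0.3-0.7, and about 17 points for discarded order at odds ratios of 1.4-1.5. These sizes rest wholly on assumed effects, correlations and grade distributions; their direction does not. The competing-death matter is a minor clarification about how absolute admission risk is displayed.

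**What to change.** - **Angina and heart-failure grade:** proportional-odds model with the enrollment grade as covariate, reporting the adjusted odds ratio with a confidence interval. Name the scales, and say that the scheduled dyspnea assessment supplies the heart-failure grade if that is intended.
- **SF-36:** ANCOVA at a named visit, or a repeated-measures model over the scheduled visits, with the enrollment score as covariate. Report the adjusted mean difference with a confidence interval.
- **Deaths:** state for both how patients who die before a visit are handled, and show mortality by arm beside the results.
- **Wilcoxon and Fisher:** keep for descriptive tables, and supply the missing variable type in the sentence.
- **Heart-failure admissions:** keep the Cox comparison and describe it as cause-specific. Show any absolute risk as cumulative incidence with death competing, not as 1-KM.

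The cost is a change of wording in the analysis section or SAP, a little more analysis work, and model assumptions to check, chiefly proportional odds. No new data, visits or patients are needed.
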